### 2.6. Outcome Measures

The primary evaluation outcome will be the change in the slope of Scr over 2 weeks. Posttreatment changes in BUN, eGFR, and urinary AKI biomarkers including urinary NGAL, IL-18, *γ*-GT, and TCM symptoms will be the secondary evaluation outcomes.

In addition to the secondary evaluation outcome, inflammatory indicators including TNF-*α* and IL-6 and oxidative stress indicators including heme oxygenase-1 (HO-1), malondialdehyde (MDA), and superoxide dismutase (SOD) will also be measured before and after treatment.

Safety outcomes and vital sign indicators (electrocardiogram, blood routine, urine routine, serum potassium, hemoglobin, etc.) will be recorded once before and 2 weeks after medication. Meanwhile, AEs will be closely observed, meticulously recorded, and properly handled by investigators throughout the study.

HCG: human chorionic gonadotropin; Scr: serum creatinine; BUN: blood urea nitrogen; eGFR: estimated glomerular filtration rate; TCM: traditional Chinese medicine; NGAL: neutrophil gelatinase-associated lipocalin: IL-18: interleukin-18; *γ*-GT: gamma-glutamyl transpeptidase; IL-6: interleukin-6; TNF-*α*: tumor necrosis factor-*α*; HO-1: heme oxygenase-1; MDA: malondialdehyde; SOD: superoxide dismutase.

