### 2.7. Evaluation Criteria for TCM Syndrome Effect

Statistics are carried out according to the improvement of clinical symptom score with reference to the *Guidelines for Clinical Research of Chinese Medicine (New Drug)* [38], and the primary and secondary symptoms of spleen-kidney qi deficiency and toxicity stasis inter-combination syndrome will be classified as mild, moderate, and severe with 4, 8, and 12 points and 2, 4, and 8 points, respectively. The two total scores calculated by the measurement scale according to TCM symptoms for each patient will be summed up, and then, they will be used to calculate efficacy indicator (EI):  EI = (total symptom score before treatment -total symptom score after treatment)/total symptom score before treatment *X* 100%  EI is adopted to evaluate the treatment efficacy after treatment. Symptom improvement levels will be demonstrated in following categories: clinical control (EI ≥ 95%), significant effect (94% > EI ≥ 70%), and effectiveness (69% > EI ≥ 30%) to inefficacy (EI < 30%).

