### 2.10. Statistical Analysis

The principal analysis will be conducted on a full analysis set (FAS), which consists of participants randomly allocated into two groups. Participants completing and complying well with the study protocol without major violation will be referred to the per-protocol population. All participants taking test drugs will be enrolled in safety analysis and conform with the ITT principle.

For non-normally distributed variables, mean ± standard deviation or median will be brought to describe continuous variables. Categorical variables will be presented in the form of numbers and percentages. The difference in Scr will be tested using the one-way ANOVA with repeated measures. The secondary outcomes will be compared between two groups using the independent-samples Student's *t*-tests for normally distributed continuous data and using Pearson's chi-square test (or Fisher's exact test if cell count <5 in any cell) for categorical data. Two-sided tests will be used for all statistical tests, and *P* < 0.05 will be considered statistically significant. SPSS (version 21.0) software will be used to carry out statistical analysis by a biostatistician not involved in the study. No additional analyses or interim analysis will be performed.

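### The four ordered TCM improvement classes fall under a chi-square/Fisher rule that ignores their order, so a significant result does not by itself show greater improvement (minor; one secondary outcome)

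*Protocol article*

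**What the plan says.** Section 2.6 lists TCM symptoms among the secondary outcomes: "and TCM symptoms will be the secondary evaluation outcomes".

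Section 2.7 builds a total symptom score, defines EI as the percentage fall in that score, and states: "EI is adopted to evaluate the treatment efficacy after treatment". It then grades EI: "Symptom improvement levels will be demonstrated in following categories: clinical control (EI ≥ 95%), significant effect (94% > EI ≥ 70%), and effectiveness", with inefficacy (EI below 30%) at the bottom. The four classes are ranked from worst to best.

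Section 2.10 gives the tests. "The secondary outcomes will be compared between two groups", by t-test if the data are continuous and normally distributed, and "using Pearson's chi-square test (or Fisher's exact test if cell count <5 in any cell) for categorical data". The level is fixed by "Two-sided tests will be used for all statistical tests, and *P* < 0.05 will be considered statistically significant". The section closes with "No additional analyses or interim analysis will be performed". It names no rank, trend or proportional-odds test, and it does not mention the TCM outcome by name.

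**The concern.** The clinical question has a direction: do symptoms improve more in one arm than in another? Pearson's chi-square and Fisher's exact test treat the four classes as unlabelled boxes. Their alternative is any difference in class shares, spread over 3 degrees of freedom when two arms are compared.

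Two things follow. A significant P value cannot be read as more improvement without inspecting the table. And if the treatment moves patients steadily up the scale, part of the test's sensitivity goes to patterns that nobody is asking about. The article's discussion hopes that the combination will improve clinical symptoms, and this is the outcome that would support that claim.

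**Working it through.** **Inputs.** From section 2.9: 54 randomised per arm and 20% loss, so 54 × 0.80 = 43.2, or about 43 evaluable. From section 2.10: two groups at a time, two-sided 0.05. The article gives no class distribution and no power figure for this outcome, so there is no stated figure to reproduce. All class shares below are assumptions. Classes run from inefficacy to clinical control.

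**1. Class order plays no part.** Take illustrative counts of 8, 16, 18, 12 against 3, 11, 22, 18 (54 per arm).

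- Chi-square: column totals are 11, 27, 40, 30, so the expected counts are 5.5, 13.5, 20, 15 in each arm. X² = 2 × (2.5²/5.5 + 2.5²/13.5 + 2²/20 + 3²/15) = 2 × (1.136 + 0.463 + 0.200 + 0.600) = 4.80 on 3 df, p = 0.187. The value is the same for all 24 orderings of the classes. Fisher's test on the same table gives about 0.20.
- Wilcoxon: mid-ranks are 6, 25, 58.5, 93.5. The first arm's rank sum is 8×6 + 16×25 + 18×58.5 + 12×93.5 = 2623. The expected sum is 54 × 109/2 = 2943. The tie-corrected variance is (54 × 54/12) × [109 − 111906/(108 × 107)] = 24134. So z = −320/155.3 = −2.06, p = 0.039.

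**2. Significance without net improvement is possible.** Take 5, 22, 22, 5 against 14, 13, 13, 14.

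- Chi-square: X² = 4 × 4.5²/9.5 + 4 × 4.5²/17.5 = 8.53 + 4.63 = 13.15 (unrounded) on 3 df, p = 0.004.
- Wilcoxon: mid-ranks are 10, 37, 72, 99, and the rank sum is 50 + 814 + 1584 + 495 = 2943, exactly its expectation, so p = 1.00.

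In simulation, with true shares 15/35/35/15% against 30/20/20/30% and 43 per arm, chi-square rejects in about 65% of trials and Wilcoxon in about 6%. With 20/30/30/20% against 30/20/20/30% the rates are about 31% and 5%.

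**3. Power under a consistent shift.** Simulated with proportional odds over three assumed control distributions (30/45/20/5%, 30/35/25/10%, 25% in each class), Pearson chi-square against tie-corrected Wilcoxon:

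| Odds ratio | 43 per arm | 54 per arm |
|---|---|---|
| 2.0 | 26–28% vs 40–43% | 33–35% vs 49–51% |
| 2.5 | 44–47% vs 62–64% | 55–57% vs 72–74% |
| 3.0 | 61–63% vs 78–79% | 72–74% vs 87–88% |

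With control shares 25/40/25/10% and odds ratio 2.5 the figures are 46% vs 64% at 43 per arm and about 56% vs 74% at 54. The loss is roughly 14 to 18 points, and 13 in the smallest case. Coding the plan's switch to Fisher when a cell is below 5 also gives 46% in the 43-per-arm case. When the arms have identical class distributions, both tests reject in about 5% of trials.

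**4. Power when the benefit is not a uniform shift.** Control shares 25/40/25/10%, 43 per arm, with no class movement downward:

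| Treated shares | Chi-square | Wilcoxon |
|---|---|---|
| 25/20/25/30% | 62% | about 39% |
| 5/60/25/10% | 65% | about 20% |
| 25/25/25/25% | 38% | 24% |

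Here the unordered test is the more powerful one.

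**The case against.** The strongest reply is that section 2.10 never ties the chi-square rule to TCM symptoms. Section 2.6 lists them alongside BUN, eGFR and the biomarkers as post-treatment changes. Section 2.7 speaks of improvement in a score and makes EI, a percentage, the efficacy measure. The classes may be there only for display. On that reading the score or EI goes to the t-test. This largely stands. It does not remove the point, because the categorical rule for secondary outcomes needs something to apply to and the article defines nothing else.

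Three stronger readings are tempting, and the documents do not support them.

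- *The TCM outcome has no directional test.* The exclusion of additional analyses does not cancel the t-test in the same section, which may apply to the score or EI if they are normally distributed.
- *Chi-square always loses power here.* Step 4 shows the reverse for benefits confined to part of the scale, and the article gives no class shares from which to choose between the patterns.
- *The rule produces false positives.* In step 2 the two arms really do differ in spread. Those tables were built to show what can happen, not what is likely, and the test holds its level when the distributions are the same. The percentages that 2.10 already requires would also show the pattern.

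It is also fair to say that chi-square on class counts is a valid test, and that detail on an ordinal secondary outcome is often left to the analysis plan. But the article does name a test for categorical outcomes, and that test discards the ranking its own section 2.7 sets up.

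**Conclusion.** The point holds as a minor one about efficiency and interpretation on a single secondary outcome. A significant chi-square or Fisher result on the four classes does not by itself establish greater symptom improvement; this follows from the tests and needs no assumption. The power loss set out in the working depends on assumed class shares and on a proportional-odds shift, and it should not be quoted without those conditions. That the rule applies to the TCM classes at all is an inference from sections 2.6, 2.7 and 2.10 read together. The primary creatinine analysis and the sample size are unaffected.

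**What to change.** In section 2.10, say which TCM variable carries the test, and choose one of two routes:

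- compare the ordered classes between groups by Wilcoxon rank-sum or proportional-odds regression; or
- make the week-2 total symptom score the tested variable, by ANCOVA with the baseline total score as covariate, and show the classes descriptively.

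Keep chi-square/Fisher for unordered or binary variables.

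The cost is one sentence, with no extra patients, visits or data, and SPSS runs these analyses. The small downside is lower sensitivity to differences that are not an overall shift. The reported class percentages would still show them.

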#### 2.3.7. Shedding Criteria

Natural shedding and loss of follow-up during observation may occur during the trial. He/she will quit by himself/herself if it is not suitable to continue participating in the trial because of severe complications or unpredictable events. Shedding cases should be documented in detail, and intention-to-treat (ITT) analysis should be performed in the end.

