### 2.9. Sample Size Estimation

The sample size will be calculated according to the primary outcome of baseline Scr change. Based on previous studies and literature reports [26, 30], the mean value of Scr was 160.39 *μ*mol/l, and the standard deviation was 44.43 *μ*mol/l. We thus hypothesize that Scr for CHF combing RG group would be significantly lower than the other two groups by more than 30 *μ*mol/l. It is calculated using the sample size estimation software PASS (version 15.0.3) to achieve test efficacy 1–*β* = 0.90 and significant difference *α* = 0.05 (one-sided test). Considering 20% drop rate, the estimated sample size for randomization will be 54 cases in each group for a total of 162 cases.

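### Section 2.10 rules out additional analyses with no exception for missing data, although the design allows for 20% loss and names a primary method that usually uses completers only

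*Protocol article*

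**What the plan says.** All places are in the protocol article.

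- **Section 2.9** builds loss into the design: "Considering 20% drop rate, the estimated sample size for randomization will be 54 cases in each group".
- **Section 2.10** sets the primary population: "The principal analysis will be conducted on a full analysis set (FAS"), made up of randomised participants. It also defines a per-protocol population. For Scr it names one method, a one-way ANOVA with repeated measures. It ends with "No additional analyses or interim analysis will be performed". No missing-data method is named.
- **Section 2.3.7** says of patients who drop out that "intention-to-treat (ITT) analysis should be performed in the end".
- **Section 2.3.6** says that withdrawn cases, including those lost to follow-up, are not analysed for efficacy. Those who withdraw within two weeks are also kept out of the per-protocol population.
- **Section 2.5** has examinations at baseline and weekly during treatment. **Table 3** marks Scr at weeks 0 and 2 only.

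**The concern.** A protocol article that is silent on missing data can leave the detail to an analysis plan. This one is not silent. It states a restriction, and an analysis plan that added a sensitivity analysis could be read as contradicting it.

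The restriction matters because of what surrounds it. Repeated-measures ANOVA in its usual form drops any patient who lacks a scheduled value. On the Table 3 schedule, a patient lost before week 2 has no Scr after baseline. The per-protocol set gives no check, because it leaves out the same early withdrawals.

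Loss could plausibly be informative. Section 2.5 gives one arm a daily infusion, another oral CHF plus enemas five times a week, and the third both. Section 2.4 says treatment cannot be blinded. Sections 2.3.6 and 2.3.7 list poor compliance, allergy, patient request and severe complications among the reasons for leaving. If leaving depends on both arm and recovery, a comparison of completers is biased for the all-randomised comparison that the full analysis set is meant to give.

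**Working it through.** **Inputs from the documents.** SD 44.43 μmol/l, power 0.90, α 0.05, 20% loss, 54 per arm (Section 2.9). Scr in the combination arm "would be significantly lower than the other two groups by more than 30" μmol/l (Section 2.9). Testing rule: "Two-sided tests will be used for all statistical tests" (Section 2.10).

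**Step 1: reproduce the 54.** Use a three-group ANOVA F test with means 160.39, 160.39 and 130.39. Deviations from the grand mean are 10, 10 and -20, with sum of squares 600. The noncentrality is λ = n × 600 / 44.43².
- n = 42: λ = 12.77, power 0.895.
- n = 43: λ = 13.07, power 0.903.
- 43 / 0.80 = 53.75, rounded up to 54.

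So 43 evaluable per arm is the design's own number, and 54 - 43 = 11 per arm (11/54 = 20.4%) are allowed to be missing.

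**Step 2: significance threshold with 43 per arm.**
- SE of a pairwise difference = 44.43 × √(2/43) = 9.58.
- Two-sided 5% threshold = t(0.975, 84) × SE = 1.989 × 9.58 = 19.05 μmol/l.

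**Step 3: effect of the missing patients.** All-randomised difference = (43/54) × observed difference + (11/54) × difference among missing patients. The SE is held at 9.58.

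| Observed difference | Difference among missing (assumed) | All-randomised difference | p |
|---|---|---|---|
| -30 (p = 0.002) | 0 | 0.796 × (-30) = -23.9 | 0.015 |
| -30 (p = 0.002) | +30 | -23.9 + 0.204 × 30 = -17.8 | 0.07 |
| -22 (p = 0.024; assumed) | 0 | 0.796 × (-22) = -17.5 | 0.07 |

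**Step 4: where the conclusion turns.** If missing patients had no benefit, the observed difference must be at least 19.05 / 0.796 = 23.9 to stay significant. Observed differences between about 19.1 and 23.9 would be significant among completers but not under that assumption.

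Put another way, let combination-arm leavers be worse than completers of their arm by δ, with comparator loss random. The difference then shrinks by 0.204 × δ, and significance is lost at:
- observed 30: δ = (30 - 19.05) / 0.204 ≈ 54 μmol/l, about 1.2 SD;
- observed 22: δ = (22 - 19.05) / 0.204 ≈ 14 μmol/l.

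**Step 5: false positives when there is no true effect overall.** Suppose combination-arm leavers are 30 μmol/l worse than stayers and comparator loss is random. Stayers then look better by the loss fraction × 30.
- 20% loss in both arms: bias 6.0, bias/SE = 0.63, and the nominal 5% test rejects about 9–10% of the time.
- 30% against 10% loss: bias 9.0, SE 9.60 with 38 and 49 observed, bias/SE = 0.94, and it rejects about 15–16% of the time.

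**The case against.** **The sentence may mean less than it says.** It may be meant only to exclude interim looks and unplanned subgroup or adjusted analyses. A reader might infer that it also bars the per-protocol analysis. The documents do not support that: Section 2.10 itself defines that population, so analysing it is plausibly part of the plan. The narrower intent is possible for missing-data checks too, but the text does not say so and names no such check among the planned analyses.

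**Completer-only analysis is inferred.** A reader might say that a complete-case result is certain to be presented as an all-randomised one. The protocol neither specifies nor forbids imputation, and Sections 2.3.7 and 2.10 point to ITT and the full analysis set. What stands is that the named method, run in its usual form, gives that result.

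**The Scr schedule is not settled.** Section 2.5 suggests weekly examinations, and the outcome is a slope. If week-1 Scr is taken, a patient lost later has some data after baseline. Standard repeated-measures ANOVA would still drop that patient for the missing week-2 value.

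**The size rests on chosen scenarios.** The 20% is a planning allowance, not a forecast. The observed 22, the 30%/10% loss and the shifts among leavers are assumptions. The +30 row is a swing of 60 μmol/l from the observed difference.

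**Some protection exists.** Reasons for withdrawal must be recorded, and Section 2.3.6 says complications that indicate AKI progression should not simply be excluded from the efficacy analysis. This limits informative exclusion but does not supply a sensitivity analysis.

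**Conclusion.** The point holds as a stated restriction that should be narrowed. As written, Section 2.10 allows no check of the primary result against informative dropout, while the design allows about 11 of 54 patients per arm to be missing.

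The documents do not show that the primary result would be overturned. At the assumed effect of 30 μmol/l it survives missing patients having no benefit, and it fails only if combination-arm leavers are about 54 μmol/l worse than completers. The exposure lies with smaller significant differences, roughly 19 to 24 μmol/l, which do not survive the no-benefit case.

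These figures assume normal data, that the Section 2.9 SD applies to the quantity compared, equal 20% loss except where stated, a pairwise two-sided 5% test, and an SE fixed at 43 per arm. They show what dropout could do, not what it is likely to do.

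**What to change.** Replace the sentence in Section 2.10 with: *No interim analysis and no unplanned analyses will be performed.* Then prespecify:

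1. One missing-data sensitivity analysis of the primary comparison on all randomised participants, for example multiple imputation by arm with a delta-adjusted tipping point. Imputation variables and step sizes can be left to the analysis plan.
2. A per-protocol analysis, labelled supportive.
3. Reporting of missing Scr by arm and reason.

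Two conflicts must be reconciled at the same time:

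- Section 2.3.6 (withdrawn and lost cases not analysed for efficacy) with Sections 2.3.7 and 2.10 (ITT and full analysis set). Otherwise the new analysis would include patients whom 2.3.6 excludes.
- Section 2.5 (weekly examinations) with Table 3 (Scr at weeks 0 and 2), because the schedule decides which values count as missing.

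The sample size stays at 54 per arm. The cost is a few sentences and modest programming. The downside is that a favourable result may have to be reported as sensitive to dropout. The change should be made before outcome data are seen, so that the check cannot look data-driven.

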### 2.11. Quality Control of Data

Before initiating the trial, a conference will be held in Shanghai to make sure all participants can receive centralized training. They will receive professional training to ensure accurate, complete, and timely recording of observations and results in the CRFs. The clinical protocol is designed on the foundation of expertise and clinical experience of all participants to ensure it is scientific and operational. Patients will be selected strictly according to inclusion and exclusion criteria, and the entire trial process will follow a multicenter randomized controlled clinical design. At each site, test sample materials including blood, urine, and other materials will be collected and delivered to the central laboratory for analysis and destruction to reduce data bias. If there are AEs during the trial, appropriate treatments should be taken for subjects and it is necessary to report the situation to authorities immediately. Biostatisticians will participate in designing the trial and analyzing collected data up to the end of the trial. Data administrators will primarily conduct manual checks of data entry and then perform systematic checks after completion. The data monitoring committee (DMC) will meet regularly to monitor the conduct of the trial and evaluate quality control of data.

### 2.12. Safety Assessment

In this trial, AEs are recognized as negative or untoward medical manifestations during the study conducting period, regardless of the possibility of a causal relationship. CHF has been applied to clinical treatments and animal experiments for many years and proved an effective prescription, and no obvious AEs have been observed. According to the package insert of RG, it may have skin rash and other allergic symptoms such as anorexia, nausea, upper abdominal discomfort, and other gastrointestinal symptoms occasionally. Relevant AEs occurring in this trial will be recorded systematically in detail throughout the trial. Meticulous description of event cause, subsequent interventions, handling outcome, and other relevant information will also be included in the form. If AEs occur, the patient will be closely observed and properly taken care of until AEs disappear. It is essential to carry out follow-up investigations. Besides, the results should be recorded in detail and then reasons will be analyzed. Serious adverse events (SAEs) are as follows: (1) critical or life-threatening complications; (2) hospitalization or disability, even death; and (3) other serious event significant hazards to participants. AEs and SAEs will be monitored and evaluated by researchers, and then, researchers will give related participants proper treatments and report them to authorities. They will also be reported in trial publications at the end of the study.

